**Caregivers' measures**					
	Self-perceived stress (PSS-14)	^a^ABI	x	x	x
	Self-efficacy ^b^(RSCS)	ABI	x	x	x
	Caregiver perception of troubles ^c^(RMBPC)	ABI	x	x	x
	Burden ^d^(ZBI)	^e^SA	x	x	x
	Self-reported health ^f^(NHP)	SA	x	x	x
	Depressive symptoms ^g^(BDI-2)	SA	x	x	x
	Knowledge about illness ^h^(VAS)	SA	x	x	x
	The quality of the relationship with the patient (VAS)	SA	x	x	x
	Time spent on caregiving ^i^(RBC)	Interview	x	x	x
	Other sources of stress (ie, work, health status, financial status) (RBC)	Interview	x	x	x
	Respite or social help (ie, psychotherapy, associations, technical help, etc) (RBC)	Interview	x	x	x
	Time and frequency using the program (website statistics)	Website	x	x	x
	Satisfaction towards the program content (weekly paper-based survey filled at home)	Weekly survey (M0-M3 for ^j^EC)	x	x	x
**Patients' measures**					
	Cognitive status ^k^(MMSE)	Medical data	x	-	-
	Degree of dependency ^I^(IADL-RBC)	Interview	x	-	-
	Duration of symptoms (RBC)	Interview	x	-	-

^a^ABI=Administered by the interviewer,^b^RSCS=Revised Scale for Caregiving Self-Efficacy, ^c^RMBPC=Revised Memory and Behavior Problem Checklist, ^d^ZBI=Zarit Burden Interview, ^e^SA=Self-administered,^f^NHP=Nottingham Health Profile, ^g^BDI-2=Beck Depression Inventory-second version, ^h^VAS=Visual Analogical Scale, ^i^RBC=Reported by caregiver, ^j^EC=Experimental condition, ^k^MMSE=Mini-Mental State Examination, ^l^IADL=Instrumental Activities of Daily Living

#### Primary Outcome Measure: PSS-14

Stress perceived by the caregiver is measured by the French version of the Perceived Stress Scale, the version of 14 items from Cohen et al [20], translated into French by Bruchon-Schweitzer in 2002 [24]. The PSS-14 is a widely used self-reported scale evaluating the general appraisal of stress in the last month. It consists of 14 items, with scores ranging from 0 (never) to 4 (very often). This scale has demonstrated a high reliability and validity in several studies [25]. The total score range for this scale is 0-56. Due to numerous roles of caregivers (as mentioned above) and in order to target stress specifically related to a caregiving role, we adapted the instruction of the PSS-14 by proceeding with hetero evaluation and adding the following text in bold: "this scale ask[s] you about your feelings and thoughts about your experience with your relative during the last four weeks." The rest of the instruction is similar to that proposed by Cohen in 1983.

#### Secondary Outcomes Measures Administered by an Interviewer

##### Self-Efficacy

The Revised Scale for Caregiving Self-Efficacy was validated in 2002 by Steffen et al [26] and translated into French by Marziali and Garcia in 2011 [27]. This scale offers a simple and effective way to evaluate caregivers’ self-efficacy on: (1) obtaining respite, (2) controlling upsetting thoughts, and (3) responding to disruptive patient behaviors. Each section has five items arranged from easiest to most difficult (based on research results) [26]. For each item the participants choose a score between 0 and 100, based on their degree of confidence for each situation. This scale should be administered by an interviewer [26].

##### Perceived Behavioral and Cognitive Problems

The Revised Memory and Behavior Problem Checklist [28] is a widely used scale that rates the caregiver’s perceived frequency of occurrence of behavioral and cognitive problems and the caregiver’s perceived distress facing these problems. It explores 24 situations in which the caregiver estimates: (1) the frequency of situations/problems during the last week, and (2) the caregiver’s response to each situation/problem. Satisfactory internal consistency coefficients of reliability have been reported (for frequency of behaviors .93 and for reaction .90) [29].

#### Secondary Outcomes Measures Self-Administered

##### Zarit Burden Interview

The Zarit Burden Interview (ZBI) is a subjective measure of burden that includes 22 items exploring the caregiver’s perception and feelings about care situations. There are three factors that could explain 56.3% of global score variance: (1) caregiver’s social and personal life, (2) psychological burden, and (3) caregiver’s guilt [30]. The score range is 0-88, a higher score indicating a higher burden level.

##### Depressive Symptoms

Depressive symptoms will be evaluated with the second version of Beck Depression Inventory [31]. This widely used scale comprises 21 items, and the total score range is 0-63 [32].

##### Self-Perceived Health

Bucquet et al [33] validated the Nottingham Health Profile in France. We use this scale to evaluate the self-reported morbidity of caregivers. There are 38 items that are grouped in 6 dimensions: (1) physical mobility, (2) social isolation, (3) emotional reactions, (4) pain, (5) sleep, and (6) energy. In the French validation study, weights were calculated using Thurstone's Paired Comparisons [33]. The addition of this item totals a hundred per dimension and corresponds to the percentage of the illness impact perceived by each individual.

#### Additional Measures

##### Caregivers' Measures

The sociodemographic variables and general information on caregiver situation collected are age, sex, educational level, relationship with the patient (spouse versus nonspouse), current psychopharmacological treatment, current psychosocial services and respite care (daycare centers for the patient, in-home care services, etc), time spent per week with the patient, and their “free time”. Moreover, the quality of the relationship with the patient, the caregiver’s confidence in his/her ability to cope with the consequences of the disease, and the caregiver’s level of knowledge about AD are evaluated with the Visual Analogical Scales.

Participants in the EC complete a satisfaction survey each week, after watching the weekly program. Therefore, qualitative information about perceived utility of this program is obtained during the face-to-face interviews in the visits M3 and M6. Moreover, the frequency and duration of the Web-based program use for each participant is stored and anonymously analyzed at the end of the study.

##### Patients' Measures

The global cognitive status of patients is evaluated with the Mini-Mental State Examination (MMSE) [34] and obtained from the patients’ medical file, if the patient accepts it (during follow-up at the Memory Center the patients with AD are evaluated with neuropsychological batteries, including the MMSE evaluation). The degree of dependency from the patient is evaluated by the French version of the Instrumental Activities of Daily Living [35] reported by the caregiver at M0, and the duration of symptoms is also based on the caregivers’ report.

#### Data Management and Statistical Analysis

##### Monitoring/Security Issues

Data are collected via an electronic case-report form, then centralized, and stored on a secured server using the “CleanWEB” system [36]. A monitoring of records is planned every two months and done by an external agent to control the respect of protocol and procedures according to Clinical Best Practices guidelines [37].

##### Ethical Proceedings

This study protocol was submitted to the French ethical CPP and received approval on July 2011. Before they enter the study, all participants receive an information sheet and sign a written consent form.

The study provides equal opportunity to access the program. Caregivers who do not meet the inclusion criteria can access the website and program as external participants. Also, every participant is asked to search another form of help (ie, that of a psychologist or a physician) if he/she feels the need to, and to report it to the main investigator.

##### Sample Size

The sample size has been calculated by the Biostatistics and Epidemiology Department of the Hôtel-Dieu Hospital (Paris). Based on the literature [38], a 6-point difference on PSS-14 scale is expected between EC and CC at the posttest evaluation (M3). With an assumed standard deviation of 9, 40 participants per group should be included to be able to detect such a difference with an 80.0% power (Cronbach alpha=.05; two-tailed).

##### Data Analysis

The Biostatistics and Epidemiology Department of the Hôtel-Dieu Hospital will perform statistical analysis. All the analyses will be conducted according to the intention to treat principle and to handle with missing data; multiple imputations will be used if the missing at random or missing completely at random hypothesis holds. Otherwise sensitivity analysis will be done. No interim analysis will be performed.

A description of the characteristics of the two groups will be performed using percentages for categorical variables and means with standard deviation for quantitative variables. For primary and secondary outcomes, student *t* tests or a Wilcoxon test if required, as well as covariance analysis to take the regression to the mean into account, will be used to compare means between experimental and control groups. Percentages will be compared using chi-square test or Fisher’s exact test if required. Calculations will be performed using SAS software.

Qualitative data obtained during visits M3 and M6 from EG participants’ perception on the program’s utility and satisfaction will be analyzed by Broca’s research team, using thematic analysis [39].

Statistical analysis will exclude data from: (1) caregivers performing less than two thirds of the online program (participant validates fewer than 8 out of 12 sessions), (2) dropouts due to mental or physical state of the caregiver becoming incompatible with this research protocol.

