## Methods

### Study Design

This is a pragmatic and unblinded randomized controlled trial (NCT01430286) of a Web-based psychoeducational program for the CGs of patients diagnosed with AD. Two parallel groups are compared. The experimental group receives immediate access to a Web-based program, and the comparison group is given the information usually delivered to the patient by the geriatrician during follow-up consultations. In addition to the baseline visit, two follow-up visits at the hospital are planned at 3 and 6 months.

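### Multiple imputation depends on a missing-at-random condition that observed data cannot confirm, and sensitivity analysis replaces it when it should accompany it

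*Protocol article*

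**What the plan says.** The only text on missing data is in the Data Analysis section of the protocol article. It declares that "All the analyses will be conducted according to the intention to treat principle", and then sets a two-branch rule: "multiple imputations will be used if the missing at random or missing completely at random hypothesis holds. Otherwise sensitivity analysis will be done". It gives no basis for deciding whether the hypothesis holds.

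The same section names the comparison of means for primary and secondary outcomes: a t test, or a Wilcoxon test if needed, together with covariance analysis. That comparison is not made conditional on the missing-data mechanism.

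The section ends by removing two sets of participants from the statistical analysis: caregivers who validate fewer than 8 of the 12 sessions, and "dropouts due to mental or physical state of the caregiver becoming incompatible with this research protocol".

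**The concern.** The rule has two faults as written.

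- **The condition cannot be verified.** Observed data can give evidence against missing completely at random (MCAR), but MCAR and MAR lead to the same branch. The branch turns on MAR against MNAR, which depends on values nobody has seen.
- **Sensitivity analysis is in the wrong place.** It is most needed when the main result relies on MAR, yet the rule calls for it only when MAR has been rejected. In that second branch it has no main missing-data handling to be compared with.

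The trial's design makes this more than a formality. The Study Design section states: "This is a pragmatic and unblinded randomized controlled trial". Caregivers therefore know their arm, and the demands differ: the experimental arm has a weekly session and survey for 12 weeks, while the control arm has usual care. The primary outcome is the caregiver's own rating of stress. Missingness that differs by arm and is related to stress is plausible, although the article does not show that it will occur. If it did occur, a report that followed the rule and accepted MAR would contain nothing to reveal it.

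**Working it through.** **Design figure.** The plan gives no figure on missing data. Its only related figure is the sample size: 40 per group for a 6-point difference, SD 9, 80% power, two-sided 0.05. The normal formula gives 2 × 9² × (1.960 + 0.842)² / 6² = 35.3, so 36 per group; the t-based calculation gives 37. The stated 40 would fit an allowance of about 10% (36 / 0.90 = 40), but no allowance is stated. The number is on the safe side, and the present point does not depend on it.

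**The rule, branch by branch.**

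| Judgement reached | Missing-data handling | Check of the assumption |
|---|---|---|
| MCAR or MAR accepted | Multiple imputation | None called for |
| MAR rejected | None defined; the t test or Wilcoxon test and covariance analysis remain | A sensitivity analysis of unstated form |

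Neither branch gives a main missing-data analysis together with a check on its assumption.

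**Illustrative size.** Higher PSS-14 means more stress, and benefit is the control mean minus the experimental mean. Let m be the share missing at M3 and d the number of points by which the missing scores are truly worse than MAR predicts. Imputation under MAR makes each arm's mean too low by m × d, so

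overstatement of benefit = (m_EC × d_EC) − (m_CC × d_CC).

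The documents give neither m nor d for either arm; all values below are assumptions.

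| Scenario | Calculation | Overstatement | Share of 6 points |
|---|---|---|---|
| EC only, 20%, d = 3 | 0.20 × 3 | 0.6 | 10% |
| EC only, 20%, d = 6 | 0.20 × 6 | 1.2 | 20% |
| EC only, 30%, d = 3 | 0.30 × 3 | 0.9 | 15% |
| EC only, 30%, d = 6 | 0.30 × 6 | 1.8 | 30% |
| EC 20%, CC 10%, d = 3 in both | 0.6 − 0.3 | 0.3 | 5% |
| Equal m and equal d in both arms | m × d − m × d | 0 | 0% |

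**Against the significance threshold.** With SD 9 and 40 per arm, the standard error of an unadjusted difference is 9 × √(2/40) = 2.01. The smallest significant difference is then 1.96 × 2.01 = 3.94 points. An estimated benefit of 4.5 points would be significant, but reduced by 0.6 to 1.8 points it becomes 3.9 to 2.7, below the threshold. This sets aside the information lost to missing data and the precision gained from covariance adjustment.

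**The case against.** Four objections have force.

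- **The rule can be operated.** Holding can be read as being judged plausible, and the trial collects information for that judgement: stressful events, patient hospitalisation, and repeated stress, burden, health and depression scores. A reader might infer that the rule cannot be executed at all, or that the choice would be made after seeing data by arm. The article supports neither: it does not say when the judgement is made or whether arm is known at that point. A condensed article may also leave the imputation model and the form of sensitivity analysis to a fuller document. What remains is the structure that the article does fix: a condition that data cannot confirm, and sensitivity analysis as the alternative to imputation.
- **A primary comparison exists.** A reader might infer that the second branch has no primary estimate. The between-group tests stand in both branches; only the missing-data handling is undefined.
- **The health-related dropouts are not covered by this rule.** It is tempting to cite them as the informative mechanism that defeats the imputation. As written they are excluded from analysis, so the imputation never reaches them. Nor does the text say that their stress rose; such dropout could be MAR given the observed scores. Any bias from removing them belongs to the exclusion rule.
- **The 10-30% range is one scenario.** It assumes missingness in the experimental arm only, and its upper departure of 6 points equals the whole target effect. Comparable missingness in the control arm shrinks the bias or removes it.

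A charitable reader could also say that the authors meant imputation under MAR with sensitivity analysis alongside. The wording makes the second an alternative to the first, so even then the text needs correcting.

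**Conclusion.** The point holds as a fault in a stated rule, not as missing detail. The choice of method depends on an unstated judgement about something the data cannot settle. When MAR is accepted, the assumption goes unchecked; when it is rejected, no main missing-data handling is defined.

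The size is unknown because no dropout rate is given. The illustration runs from zero, with equal missingness and departure, to 1.8 of the 6 target points, with 30% missing in the experimental arm only and a 6-point departure. The upper part of that range could change whether a borderline result is significant. The fault does not invalidate the design, but it should be corrected because it limits how far the primary result can be trusted.

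The two exclusions are a separate conflict with the declared intention-to-treat principle. They bear on this point because correcting the imputation rule alone would leave those caregivers outside the analysis.

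**What to change.** Replace the conditional rule with wording to this effect: *Missing M3 PSS-14 scores will be handled in the main analysis by multiple imputation under a missing-at-random assumption, using arm, PSS-14 at M0 and M6, gender, relationship and at most a few baseline scores. Whenever outcome data are missing, a sensitivity analysis under missing-not-at-random departures will be reported, for example a delta-adjusted tipping-point analysis with the shift allowed to differ by arm.*

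The model should stay small. With 40 per arm and, for illustration, 20-30% missing, only 28 to 32 caregivers per arm would have an observed M3 score, too few to support separate imputation models by arm with every baseline secondary score. The tipping-point analysis is one acceptable choice among several; what matters is that some departure from MAR is always examined.

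Separately, remove both exclusions (fewer than 8 of 12 sessions, and health-related dropout) from the main analysis. An analysis restricted to adherent caregivers can be kept if labelled as supplementary.

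The cost is a few sentences and modest extra SAS programming. The proposed variables are already scheduled for collection: PSS-14 at all three visits, the stratification factors and the baseline scores.

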### Randomization

A computer-generated randomization list is used to assign the participants in the experimental condition (EC) group or in the control condition (CC) group after assessment with PSS-14 and all the inclusion and noninclusion criteria are checked. Blocking and stratification by gender and relationship (spouses versus nonspouses) were used to generate the randomization list.

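### Randomization is stratified by gender and spouse/nonspouse, but the stated between-arm tests do not use these strata; if either factor predicts the outcome, the tests are conservative and some precision is lost

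*Protocol article*

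**What the plan says.** On allocation, the Randomization section of the protocol article says: "Blocking and stratification by gender and relationship (spouses versus nonspouses) were used to generate the randomization list". Two binary factors give four strata.

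On analysis, the Data Analysis section sets one group of methods for the primary and secondary outcomes together. It names a Student t test, replaced by a Wilcoxon test where needed, and then adds a third method: "as well as covariance analysis to take the regression to the mean into account, will be used to compare means between experimental and control groups". No covariate is listed. Regression to the mean points to the baseline score, but even that is inferred. Neither stratification factor appears in the section. Relationship returns only under Strengths of the Study, as an exploratory question about whether spouses or nonspouses benefit more. That is not an adjustment of the arm comparison.

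On size, the Sample Size section expects a 6-point PSS-14 difference at M3 and gives the group size: "With an assumed standard deviation of 9, 40 participants per group should be included". The target is 80% power in a two-sided test at .05.

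**The concern.** Blocking within strata makes the arms nearly equal in gender and relationship. Differences between strata then hardly contribute to the true variability of the arm difference. A two-sample t test or an ordinary Wilcoxon test still counts that variation as error. If either factor predicts the outcome, the reported standard error exceeds the true one, the interval is wider than it need be, and the test rejects less often than its nominal level. A covariance analysis on baseline alone has the same fault for whatever part of the stratum effect the baseline score does not capture.

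What is at stake is precision in a trial of 80 caregivers. Both factors are known before randomization, so any loss is avoidable.

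**Working it through.** **Inputs from the documents.** 40 per group, SD 9, difference 6 points, two-sided .05 (Sample Size); 80 in total (Abstract); stratification by gender and relationship (Randomization).

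**Assumptions, because the documents are silent.** The share R² of outcome variance explained by the strata is varied from 0 to 20%. The simulations use blocks of 4. Stratum sizes are either 70% women and 50% spouses, or cells of 35/15/15/35%. For the covariance analysis, the correlation between baseline and M3 is 0.5 (baseline explains 25% of variance). All 80 caregivers are analysed.

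**The plan's own figure.** n per group = 2 × (1.96 + 0.84)² × 9² / 6² gives 36 (normal approximation), or 37 with the t distribution. With 40 per group, SE = 9 × √(2/40) = 2.01, and power is 84.6% (normal) or 83.8% (t). The stated 40 is therefore not reproduced at exactly 80% power. A 10% dropout allowance would give it (36/0.9 = 40), but none is stated. This gap does not bear on the present point.

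**The t test, by formula.** With balance inside strata:
- true SE = 2.01 × √(1 − R²), while the t test goes on reporting about 2.01
- actual type I error = 2 × [1 − Φ(1.96/√(1 − R²))]
- power of the unadjusted test = Φ[(6/2.01 − 1.96)/√(1 − R²)]
- power with strata in the model = Φ[6/(2.01 × √(1 − R²)) − 1.96]

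| R² | True SE | Type I error, t test | Power, t test | Power, with strata | Loss (points, before rounding) |
|---|---|---|---|---|---|
| 0% | 2.01 | 5.0% | 84.6% | 84.6% | 0 |
| 5% | 1.96 | 4.4% | 85.3% | 86.4% | 1.1 |
| 10% | 1.91 | 3.9% | 85.9% | 88.2% | 2.2 |
| 20% | 1.80 | 2.8% | 87.3% | 91.5% | 4.2 |

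**The t test, by simulation.** Two separate simulations agree with the formula. At R² = 20%, type I error is 2.7% and 2.9%, and power is 85.4% and 86.2% against 90.6% with strata in both. At R² = 0, power is 83.5% against 83.6% in one and 83.7% against 83.6% in the other, so adjustment costs nothing visible. For a true effect of 5 points, power is 70%, 70% and 71% unadjusted against 72%, 74% and 79% adjusted, at R² of 5%, 10% and 20%.

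**Covariance analysis on baseline.** The loss depends on how the strata relate to the baseline score. Power at 6 points, baseline only against baseline plus strata:
- *Strata shift baseline and M3 equally.* 91.7% against 91.8%, 92.8% against 93.2%, and 92.9% against 94.0%, at R² of 5%, 10% and 20%. A second run at 20% gave 93.4% against 94.3%. Type I error of the baseline-only model is 4.3%, 5.0% and 4.4%. Its simulation error over 5,000 runs is about √(0.05 × 0.95/5000) = 0.3 points, so these three values show no trend.
- *Baseline covariate unrelated to the strata.* At 20%, 94.9% against 97.7%, with a type I error of 2.7% and a reported SE of 1.75 against a true value of about 1.51.
- *Strata affect M3 only.* At 20%, 93.0% against 96.5%, the largest loss found (3.5 points).

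**The case against.** The strongest objection is that the article names a covariance analysis without listing its covariates. A stated purpose is not a complete model, and the covariate list is commonly left to a statistical analysis plan, which is not shown here and could include both factors. This stands for the covariance analysis: one cannot say that the sponsor has decided to leave the strata out. It does not stand for the t test and the ordinary Wilcoxon test, which are named for the primary and secondary outcomes and cannot carry strata.

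The second objection concerns size. Comparing the t test with a stratified model overstates the loss if the covariance analysis is what counts. When the strata act equally on baseline and follow-up, adding them gains about 1 point or less at 6 points, and at most 2.4 points for a 5-point effect. At a baseline correlation of 0.6 the gain is 0.1 to 0.8 points. This stands, and is why the range is given for both analyses.

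A reader might also extend the point to the sentence "Percentages will be compared using chi-square test or Fisher’s exact test if required" and ask for stratified tests there. The documents do not support that. The named primary and secondary outcomes are all numeric scores, and no binary efficacy outcome is defined.

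**Conclusion.** The point holds in conditional form. The design uses gender and relationship; the t test and Wilcoxon test as named ignore them, and the covariance analysis is justified only by regression to the mean. If either factor predicts a score, the reported standard error for that score is too large. For strata explaining 0 to 20% of variance, the loss at 6 points is about 0 to 5 points of power for the t test and about 0 to 3.5 points for baseline-adjusted covariance analysis.

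A reader might infer that precision is certainly lost, and in every secondary comparison. The documents do not support this: they do not say that gender or relationship predicts any outcome, and at 0% explained nothing is lost. Nor does it follow that the trial is underpowered or its conclusions unsafe. The unadjusted t test stays at about 84% or more for 6 points in every scenario with all 80 analysed, above the planned 80%, and the error is conservative and leaves the estimate unbiased.

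The weight is minor to moderate. This is an almost free improvement, not a flaw that threatens the result.

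**What to change.** In the Data Analysis section, state that the between-arm comparison of PSS-14 and of each secondary score is the covariance analysis with the baseline value of that score, gender, and relationship (spouse/nonspouse) as covariates. Where a rank test is needed, use the stratified (van Elteren) Wilcoxon test in place of the ordinary one. Include both factors in the multiple-imputation model, so that it matches the analysis. Leave the chi-square and Fisher sentence as it is.

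The cost is one sentence and two degrees of freedom: with 80 caregivers the residual degrees of freedom fall from 77 (intercept, arm, baseline) to 75. Both factors are already collected, the methods are standard in SAS, and no added participants or visits are needed.

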Participants involved in experimental group have to validate one session per week during 12 weeks (about 10 minutes per session), and complete a satisfaction survey corresponding to each session. During the first evaluation (M0) the participant is trained by a psychologist in how to use the website. At the second visit (M3) the participant is requested to provide the satisfaction paper-based survey filled out.

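### The plan promises intention to treat for all analyses, then excludes low users of the program, who can exist only in the experimental arm, and health-related dropouts

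*Protocol article*

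**What the plan says.** Everything at issue stands in the protocol article, mostly in its Data Analysis section.

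- The principle: "All the analyses will be conducted according to the intention to treat principle".
- Missing data: "multiple imputations will be used if the missing at random or missing completely at random hypothesis holds", and otherwise a sensitivity analysis.
- First exclusion, at the end of the same section: "Statistical analysis will exclude data from: (1) caregivers performing less than two thirds of the online program", with the threshold given as "participant validates fewer than 8 out of 12 sessions".
- Second exclusion: "dropouts due to mental or physical state of the caregiver becoming incompatible with this research protocol".

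No primary, secondary, per-protocol or sensitivity label is attached to the exclusions. Under Experimental Condition, "Participants involved in experimental group have to validate one session per week during 12 weeks". Under Control Condition, controls get their access code only when their participation ends. Study Design describes the trial thus: "This is a pragmatic and unblinded randomized controlled trial".

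**The concern.** An intention-to-treat analysis keeps every randomized caregiver in the arm assigned. A rule that drops people for what they did after randomization is a different analysis, and the section prescribes both without saying which comparison each governs.

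The first exclusion is asymmetric. It sets experimental-arm completers against a control arm to which no such filter applies, so the groups are no longer those that randomization formed. The second names no arm and may remove people from either. It takes out caregivers whose mental or physical state worsened, which is related to the primary outcome (perceived stress) and to the secondary outcomes of depression and self-perceived health. Where their outcomes are missing, these are cases that the imputation plan should cover. They cannot be both imputed and excluded.

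At stake is the primary comparison. The effect of being offered the program, which a pragmatic trial sets out to estimate, would be replaced by a contrast between selected groups. In an unblinded trial, leaving both rules in place also allows the choice between them to be made after the data are seen.

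**Working it through.** **Which arm the first rule acts on.** Sessions are validated only in the experimental arm, and controls have no site access before the end of their participation. Read literally, the rule would remove every control, since all have validated none. That cannot be meant, so it acts on the experimental arm alone.

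**The plan's own figure.** Inputs from Sample Size: difference 6 points on the PSS-14 at M3, SD 9, two-sided alpha 0.05, power 80%, 40 per group.

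- n per group = 2 × (1.960 + 0.842)² × 9² / 6² = 35.3, so 36. The t-based solution is 36.3, so 37.
- The stated 40 is therefore slightly generous. It would match 36 / 0.9 = 40, a 10% allowance, but no dropout rate is stated.
- Power with 40 per arm is 83.8% by t test (84.6% by normal approximation).

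**Bias from the first rule under no true effect.** Let q be the share of the experimental arm below 8 sessions, and g the amount by which their mean M3 PSS-14 would exceed that of completers. Neither is in the article, so both are assumptions.

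- With completers' mean m, the whole experimental arm has mean (1 − q)m + q(m + g) = m + qg.
- With no effect, the control arm has the same mean, m + qg.
- Completers minus controls = m − (m + qg) = −qg. A negative value favours the program.

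Type I error comes from simulation: 20,000 trials per cell, 40 randomized per arm, total SD 9, two-sided t test at 0.05, control arm kept whole. Each cell gives the bias in points, then the type I error.

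| g (points) | q = 20% | q = 30% | q = 40% |
|---|---|---|---|
| −3 | +0.6; 5.9% | +0.9; 6.8% | +1.2; 7.8% |
| 0 | 0; 5.0% | 0; 5.0% | 0; 5.2% |
| 3 | −0.6; 5.8% | −0.9; 6.9% | −1.2; 7.9% |
| 6 | −1.2; 8.7% | −1.8; 12.8% | −2.4; 17.6% |

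When g is positive, nearly all the excess false positives favour the program. At q = 30%, g = 6, they make up 12.5 of the 12.8 percentage points.

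**Power at the planning values** (6 points, SD 9, t test, first rule only):

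- 40 v 40: 83.8%
- 32 v 40 (q = 20%): 79.2%
- 28 v 40 (q = 30%): 76.0%

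The margin over the stated 80% is used up once about a fifth of the experimental arm is excluded. The second rule was not modelled, because the article gives no basis for how its dropouts would divide between arms.

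**The case against.** The best defence is that the closing paragraph describes a per-protocol set that a fuller protocol or analysis plan keeps apart from the main analysis. That is possible, but this is not a detail left out for brevity. The article states the exclusion without a label, alongside a sentence that claims all analyses for intention to treat. As written, the two conflict.

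The second line of defence concerns direction, and it largely stands. A reader might infer that the exclusions necessarily bias the result toward the program, against an untouched control arm. The documents do not support that.

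- No non-completion rate and no stress gap is given.
- Distance-Based Interventions names difficulty in scheduling and attending sessions as the main reason for moving the parent program online. Non-completion may therefore reflect lack of time rather than stress.
- Entry requires only 12 or more on a 0 to 56 scale, so mildly stressed caregivers can enroll and may stop because they need the program less. The table shows the bias vanishing or reversing in such cases.
- The second rule can remove deteriorating controls as well, which could work against the program.

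The power loss is also modest: 1 to 4 percentage points below the stated 80% in the scenarios shown.

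**Conclusion.** The contradiction is established from the text alone, and so is the one-arm action of the first exclusion. Both hold whichever way the bias runs: the comparison is no longer the randomized one, and the declared intention-to-treat effect is not what would be estimated.

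A bias favouring the program is the likelier direction, because caregivers who stop are plausibly the more strained. That is a judgement about behaviour, not a statement in the article. Under the assumed gap of 6 points, exclusion of 20% to 30% of the experimental arm produces a spurious benefit of a fifth to just under a third of the 6-point target (1.2/6 = 0.20; 1.8/6 = 0.30). The point affects the primary analysis and should be corrected before the data are analysed.

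**What to change.** Delete both exclusions from the primary and secondary analyses. State that all 80 randomized caregivers are analysed in the arm assigned, with missing outcomes handled by the imputation plan already described. Keep the 8-of-12 threshold for two purposes only: describing adherence, and a per-protocol analysis clearly labelled as supportive.

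A complier-average analysis with compliance cut at 8 sessions is not recommended as a substitute. It assumes that assignment has no effect on those below the cut, yet a caregiver who validated 1 to 7 sessions has still received content and had access to the relaxation material and forum.

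The cost is a wording change and minor analysis code. M3 and M6 visits are already planned for both groups, and nothing in the article says that they stop when a caregiver stops using the site. The drawback is that the estimate may be diluted by non-adherers. That dilution belongs to the effect of offering the program, which is what a pragmatic trial is meant to measure.
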